### Study participants

Phase 1 workshop participants will be purposively selected hospital clinicians (doctors, pharmacists and nurses), primary care clinicians (GPs, community and credentialed pharmacists), and healthcare consumers, all having discharge medicine handover experience as either a clinician or end-user. Participants will be selected to ensure maximum variation (age, professional experience, role, gender). Allocation of participants to each group will be done in advance to avoid power imbalances [47].

Phase 2 will involve purposively selected hospital and primary care clinicians, managers and department heads, and software vendors to develop the intervention and handover guidelines/material for hospital and primary care clinicians. The digital solution will be pilot tested on selected general practices, community pharmacies, and a participating hospital.

The Australian Institute of Health and Welfare census data will be used to obtain population data for the areas serviced by the various hospitals to determine the number of suburbs for each hospital service area. Phase 3 will identify community pharmacy clusters whose population catchments, based on the suburb postcodes, capture community dwelling patients with high rates of 30-day readmission to hospital. Pharmacies and GP practices within those clusters will be invited into the study. Only pharmacies who consent to being involved will be recruited into the study. Once all pharmacies have consented, each pharmacy hub will be randomised to a different step in the stepped wedge design which will determine how long each hub will be in the control and intervention phase. The pharmacist navigator at each hospital will triage patients at risk of hospital readmission due to potential MRH by means of a risk stratification processes, use of local electronic medication record dashboards, and liaison with inpatient unit/ward pharmacists, nurse navigators, and other hospital clinicians.

Patients at risk of hospital readmission (according to the study developed risk stratification process) will be approached to be recruited to the study through the pharmacist navigator at each participating hospital.

Inclusion criteria:Ability to understand and the willingness to sign a written informed consent documentAge ≥ 18 years

Exclusion criteria:Receiving chemotherapyDischarging to an aged care facilityReceiving palliative care

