The pharmacist navigator will use the risk stratification information to facilitate a structured handover of medicine information to patients’ community pharmacies, GPs, and credentialed pharmacists to trigger appropriate MMR services (Figs. 4 and 5).

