### Data analysis

Phase 1 and 2 qualitative data will be thematically analysed [57, 58]. Audio recordings will be professionally transcribed verbatim by an independent party and the transcripts quality screened and cross-referenced. The NVivo© software (QSR International Pty Ltd, Chadstone, Australia) will be used for coding by two coders. Where there are differing interpretations, the differences will be discussed between the members of the research team until consensus is reached. Data will be thematically analysed to identify underlying themes.

All phase 3 participants (excluding those recruited in the lead-in phase) will be included in the analysis. Each cluster will be classified as being in the intervention or the control phase based on their pre-specified randomised crossover time, regardless of whether crossover is achieved at that time. In the primary analysis, overall differences in readmissions will be modelled using a mixed effects Poisson regression model with a random effect for cluster (pharmacy) and a fixed effect for each step to account for any secular trend. Secular trends may include seasonal variation in readmissions or changes in practice (outside of the project’s control). We also intend to allow for both levels of clustering at the analysis stage, i.e. we will allow for both clustering by hospital and clustering by pharmacy (the unit of randomisation). This will be achieved by including both a random effect for community pharmacy hub and a random effect for hospital. Robust standard errors will be used to allow for the misspecification of the error structure when using the Poisson model to model binary events. We will report treatment effects both on the relative and absolute scale. We will also report estimates of intra cluster correlations. Secondary analysis will be conducted using similar techniques. The primary and secondary outcomes will be considered significant at the 5% level, and 95% confidence intervals will be reported. Missing outcome data is likely to be minimal for this study as it is routinely collected through hospital records. If the level of missing patient characteristic data is above 5%, we will use multiple imputation methods which allow for clustering and time effects. We will not conduct an interim analysis.

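### The stated primary model has no patient-level term, although patients are recruited after pharmacies are randomised and the same paragraph plans imputation of patient characteristics that the model does not use

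*Protocol article*

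**What the plan says.** The Data analysis section of the protocol article specifies the primary analysis as "a mixed effects Poisson regression model with a random effect for cluster (pharmacy) and a fixed effect for each step". It then allows for clustering at two levels by "including both a random effect for community pharmacy hub and a random effect for hospital", with robust standard errors. The treatment term is implied, since treatment effects are to be reported. The abstract repeats the pharmacy and step terms. No patient-level term is listed in either place. For other analyses the section says only: "Secondary analysis will be conducted using similar techniques".

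On missing data, the same paragraph first says "Missing outcome data is likely to be minimal for this study as it is routinely collected through hospital records" and then "If the level of missing patient characteristic data is above 5%, we will use multiple imputation methods which allow for clustering and time effects". It does not name the analysis that the imputed characteristics would enter.

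On recruitment, the Study participants section has pharmacies consent and then be randomised to steps. Patients come later: "Patients at risk of hospital readmission (according to the study developed risk stratification process) will be approached to be recruited". The approach is made through the pharmacist navigator at each hospital, and written consent is required. The navigator also takes part in the intervention: "The pharmacist navigator will use the risk stratification information to facilitate a structured handover".

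**The concern.** Randomising pharmacies to steps protects the comparison of pharmacies and calendar periods. It does not by itself protect the mix of patients enrolled afterwards. Here the person who triages and approaches patients also delivers the intervention. The article describes blinding for the panel that judges readmissions, not for the recruiter. The formal eligibility criteria are broad, and index admissions may arrive by any pathway, so baseline risk is likely to vary widely among eligible patients. If the kind of patient approached or consenting changes when a pharmacy crosses over, that change is confounded with treatment.

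Prespecified patient covariates would remove the measured part of such a change. The imputation sentence suggests that patient characteristics were expected to enter some analysis, but the published model gives them no place. At stake are a possible shift in the primary rate ratio and an imputation rule with no stated object.

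**Working it through.** **1. Model terms against the possible source of imbalance**

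- Step fixed effects remove calendar changes common to all pharmacies.
- Pharmacy and hospital random effects address stable differences between sites.
- Neither removes a change in patient mix that occurs within a pharmacy at its own crossover.
- Robust standard errors change the stated uncertainty, not the point estimate.
- Multiple imputation of patient characteristics has no effect on a model that contains none. The outcome itself is expected to be nearly complete.

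**2. The plan's own figures**

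- Sample size: 20 clusters × 10 patients per month × (12 − 1) months = 2200, which reproduces the stated total. After the stated 20% dropout, 8 patients per cluster-month remain: 20 × 8 × 11 = 1760.
- Planned effect: 5% / 10% = rate ratio 0.50.

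**3. Size of a case-mix shift (assumed inputs)**

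Take no true effect, a 10% control rate, and a binary risk marker with rate ratio r. Its prevalence is a in control patients and b in intervention patients. The crude rate ratio is then

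RR = [1 + b(r − 1)] / [1 + a(r − 1)].

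With a = 50%:

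| r | b = 45% | b = 40% | b = 30% |
|---|---|---|---|
| 1.5 | 1.225/1.25 = 0.98 | 1.20/1.25 = 0.96 | 1.15/1.25 = 0.92 |
| 2 | 1.45/1.5 = 0.97 | 1.40/1.5 = 0.93 | 1.30/1.5 = 0.87 |
| 3 | 1.90/2 = 0.95 | 1.80/2 = 0.90 | 1.60/2 = 0.80 |

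The cell r = 3, b = 40% corresponds to strata with 15% and 5% risk: 0.5 × 15% + 0.5 × 5% = 10% in control and 0.4 × 15% + 0.6 × 5% = 9% in intervention. Within each stratum the rate ratio is 1.00, so adjustment for the marker removes the whole of this artefact. A shift in the other direction (b = 60%) gives 1.04, 1.07 and 1.10 for the three values of r, which would hide a benefit. The formula is a crude comparison and does not simulate the full stepped wedge model.

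**4. Precision (assumed inputs)**

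The number of steps is not in the text and the design figure is not shown, so 5 or 10 evenly spaced steps were assumed. The variance is that of a linear mixed model for a stepped wedge design, with ICC 0.15, a risk difference of 0.05, two-sided alpha 0.05, one excluded month per cluster and 8 analysed patients per cluster-month. Power = Φ(0.05/SE − 1.96). Adjustment is approximated by multiplying the SE by √(1 − R²).

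| Assumed steps | SE | No covariate | R² = 2% | R² = 10% |
|---|---|---|---|---|
| 5 | 0.0219 | 0.625 | 0.634 | 0.671 |
| 10 | 0.0214 | 0.649 | 0.657 | 0.694 |

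The gain is about 1 to 5 percentage points. The power levels depend on the assumed layout and serve here only as a base for measuring the change.

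**The case against.** The strongest objection is that this is a journal article and the statistical analysis plan is not at hand. Covariate lists are commonly left to that plan, and nothing in the article says that adjustment is excluded. The imputation sentence may even point to an adjusted analysis described there. This stands against reading the article as ruling out adjustment. It does not restore consistency: the article lists the primary model's terms and gives a rule for data that those terms do not use. If the analysis plan adds covariates, the published model is incomplete. If it does not, the rule has no stated use.

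A reader might also infer that every patient carries a risk score that could simply be added to the model. The article does not support this. It describes a stratification process, dashboards and liaison with ward staff, used to decide whom to approach. It mentions no numeric score and does not say that the result is recorded alike in both phases. The navigator also applies it, so a rating made with the phase known could itself be affected by the phase, and adjusting for it could add bias. Since all enrolled patients were selected as at risk, its range may also be narrow. These points stand and limit the fix.

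Finally, chance differences in case mix between small cluster-months are not bias. They are sampling error, and the rate ratio is not distorted by leaving out a balanced covariate. This also stands: the argument rests on differential recruitment alone.

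**Conclusion.** The point holds in a limited form. The published primary model contains no patient characteristic, the imputation rule in the same paragraph has no place in it, and the way patients are recruited makes a case-mix difference between periods plausible.

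Under the assumed marker strengths and prevalence shifts that favour the intervention, the spurious rate ratio runs from 0.98 to 0.80. That would not by itself produce the planned 0.50, but it could matter if the true effect is modest. The documents do not show that such a shift will occur or how large it would be, so it should not be read as a demonstrated bias. The case for adjustment is protection against measured imbalance, because the precision gain is small. Adjustment does nothing for selection on unmeasured features. The change is advisable, but its absence does not invalidate the design.

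**What to change.** In the Data analysis section, or in the analysis plan with the article's model description aligned to it:

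- Add to the primary model a short prespecified set of objective baseline characteristics taken from the hospital record: age, and index admission pathway (emergency versus planned).
- Report the model without these terms as a supporting analysis.
- Include the risk stratification category in the primary model only if it is recorded the same way in both phases and is not open to influence from knowledge of the phase. Otherwise use it in a sensitivity analysis.
- State that the 5% multiple imputation rule applies to these covariates and to the analysis that uses them.

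The cost is a wording change, a little more analysis work and some imputation if the threshold is passed. Both core covariates should be obtainable from the hospital records that supply the outcome, but their routine capture should be confirmed. The wording should be settled before outcome data are examined and, if the planned dates allow, before first enrolment.

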## Discussion

Stakeholders and end-users will be engaged to the co-design of a multifaceted intervention that will follow the patient’s transition of care, thus placing the patient at the centre of care. The proposed intervention will utilise transition of care strategies already in place to send discharge medicine handover information to GPs whilst introducing a risk stratification process to determine the medicine information handover to community pharmacies. There will be a pharmacist navigator at each of the trial hospitals who will be an experienced clinical pharmacist, embedded at hospital sites and with access to patients’ medical records, to facilitate handover to primary care clinicians.

The evaluation of the post-discharge medication review service in community pharmacies will provide insights into this model of care for national roll-out, as was the case in the UK [63, 64]. The digital solution and information technology capability will be translatable to other service areas, including the primary care management of patients with chronic conditions and other professional pharmacy services to enable seamless interdisciplinary team-based care.

## Trial status

This trial is registered with the Australian New Zealand Clinical Trials Registry: ACTRN12624000480583p, registered 19 April 2024, https://www.anzctr.org.au/ACTRN12624000480583p.aspx. Phase 1 recruitment commenced June 2024; phase 3 recruitment will be completed by 30 September 2026.

## Trial governance

The University of Queensland is the Primary Sponsor of the trial. Secondary Sponsors are partner organisations GCHHS, MSHHS, Monash University, Sydney University, Curtin University, Bond University, and the Pharmaceutical Society of Australia. Our steering committee consists of four CIs (CI [name], CI [name], CI [name], CI [name]), one representative from each partner organisation, and includes key stakeholders such as hospital site representatives and a nominee from the consumer reference group. The steering committee provides technical advice on the project design, implementation, and analysis into the operational unit and project leadership group. Meetings are every 4 months. Any proposed changes to the project protocol will be discussed with the steering committee and if supported will be communicated to the Medical Research Future Fund as the funding agency and the primary and secondary sponsors whilst going through the ethics amendment process.

The safety committee will be six-member a group independent from the research team to identify and make recommendations on project safety issues throughout the project. Members will be recruited from the GCHHS and MSHHS Human Research Ethics Committees. The safety committee will conduct monthly trial audits and report on harms potentially associated with the intervention, e.g. if a patient’s nominated community pharmacy does not provide the intended MMR service and the patient suffers medication-related harm. The safety committee will provide advice to the project leadership group. This committee will meet every 4 months or more regularly as needed throughout phase 3.

The primary author of this manuscript is the contact for public and scientific queries. Deidentified trial participant-level data will not be shared.

## Dissemination

The results of this study will be published in peer-reviewed journals, locally through university and hospitals’ publicity channels, and be presented at academic conferences. We will follow the International Committee of Medical Journal Editors rules for authorship.

## Data Availability

All trial data will be deidentified and stored securely at GCHHS for the required period of 15 years from the end of the trial. Any data required to support the protocol can be supplied on request to the corresponding author.

## Abbreviations

GCHHS: Gold Coast Hospital and Health Service
GP: General practitioner
ieMR: Integrated electronic Medical Record
MMR: Medication management review
MRH: Medication-related harm
MSHHS: Metro South Hospital and Health Service
PSA: Pharmaceutical Society of Australia
SW-CRT: Stepped wedge cluster randomised controlled trial
WHO: World Health Organisation
